#### Secondary outcome

##### Adequate relief (AR)

Participants will receive 12 call visits (weeks 1–12) and the following question will be asked: “In the past week, have you had adequate relief of your irritable bowel syndrome pain and discomfort?”. Participants only need to answer “yes” or “no.” Responder is defined as a “yes” answer to the aforementioned question for at least 6 of the 12 weeks. AR will be accessed at week 12.

##### Irritable Bowel Syndrome-Quality of Life Questionnaire (IBS-QOL)

IBS-QOL reflects the union of the physical and mental well-being covering eight dimensions, which will be assessed at baseline, week 4, week 8, week 12, and week 20.

##### Long-term efficacy assessment

Participants will be followed up for long-term effectiveness 2 months after the treatment period (week 20). IBS-SSS response rate and IBS-QOL will be evaluated.

### Mechanistic outcome

We will analyze the whole transcriptome profiling of intestinal mucosae from the TXYF granule group (*n* = 10) and placebo group (*n* = 10) at baseline and week 12 and healthy subjects (*n* = 10) at baseline. The whole set of transcriptional deviations including mRNA, miRNA, lncRNA, circRNA, and functional networks of ncRNAs and mRNAs in IBS-D will be disclosed, which makes us to seek for the underlying molecular mechanisms and find out specific diagnostic biomarker. Meanwhile, therapeutic targets and pathways about TXYF in IBS-D will be clarified. On an Illumina Hiseq 2000 platform, the preparation of whole-set transcriptome libraries and deep sequencing will be executed by Novogene Bioinformatics Technology Cooperation (Beijing, China).

### Safety outcome

The participant will receive relevant laboratory test at baseline and week 12, including liver and kidney function (ALT, AST, Scr, BUN), blood routine test, urine routine test, and fecal occult blood test. The other tests include electrocardiograph examination.

### Adverse events

Adverse events (AEs) defined as any unpredictable and unexpected nocuous effects resulting from TXYF granule or placebo granule throughout the trial will be recorded in detail by a research assistant, including symptom, sign, severity, start date, duration, laboratory result, intervention, and outcome at every visit. Once severe adverse events (SAEs) occur, it must be immediately reported to the principal investigator, the ethics committee of the hospital, and the Guangdong Food and Drug Administration within 24 h and subject safety should be the priority. If necessary, the principal investigator has the right to terminate this trial.

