**Discussion:**

This trial will prove the effectiveness and safety of TXYF granule with high-quality evidence and provide a penetrating and comprehensive perspective on the molecular mechanism of IBS-D by whole transcriptome analysis, which makes us pinpoint specific biomarkers of IBS-D and therapeutic targets of TXYF.

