### Randomization and blinding

Randomization scheme that generates a list of 120-case randomization sequence utilizing the stratified block randomization method by computer will be implemented by an independent statistician, which guarantees that enrolled patients will be evenly allocated to the TXYF granule group or the placebo group. Then, 10 participants of each group will be randomly selected for RNA sequencing and whole transcriptome analysis. Concealment of allocation code relies on an opaque envelope. This trial requires that all participants and researchers involved in drug distribution, outcome evaluation, and data analysis are completely blinded to allocation. The occurrence of severe adverse events or other unpredictable events allows unblinding under the permission of the principal investigator.

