## Abbreviations

IBS: Irritable bowel syndrome
TCM: Traditional Chinese medicine
IBS-D: Diarrhea-predominant irritable bowel syndrome
BM: Bowel movements
TXYF: Tong-Xie-Yao-Fang
ncRNAs: Noncoding RNAs
IBS-SSS: IBS-Symptom Severity Score
AR: Adequate relief
IBS-QOL: IBS-Quality of Life Questionnaire IBS-QOL
GMP: Good Manufacturing Practices
eCRF: Electronic Case Report Form
RNA-seq: RNA sequencing
qRT-PCR: Quantitative real-time PCR
FPKM: Fragments per kilo-base of exon per million fragments mapped
GO: Gene Ontology
KEGG: Kyoto Encyclopedia of Genes and Genomes
AEs: Adverse events
SAEs: Severe adverse events
EDC: Electronic data collection
SOP: Standard Operating Procedures
ITT: Intention-to-treat

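### The adverse event definition makes unexpectedness and causation by the granule conditions for recording, so untoward events can go unrecorded and the between-arm AE comparison is weakened

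*Protocol article*

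**What the plan says.** Under Adverse events, the protocol article states that adverse events "defined as any unpredictable and unexpected nocuous effects resulting from TXYF granule or placebo granule throughout the trial will be recorded". A research assistant does the recording, and the items captured are listed as "including symptom, sign, severity, start date, duration, laboratory result, intervention, and outcome at every visit". Neither causality nor expectedness is on that list.

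The same section sets the rapid route: "Once severe adverse events (SAEs) occur, it must be immediately reported to the principal investigator, the ethics committee of the hospital", with the provincial drug regulator also named and a limit of 24 hours. The abbreviation list gives "SAEs: Severe adverse events", and Randomization and blinding says "The occurrence of severe adverse events or other unpredictable events allows unblinding", subject to the principal investigator's permission.

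Safety is a declared aim in the Abstract and at the end of the Background. The Abstract's discussion adds: "This trial will prove the effectiveness and safety of TXYF granule with high-quality evidence". Other safety data are planned separately. Safety outcome lists liver and kidney function, blood, urine and fecal occult blood tests at baseline and week 12, and an ECG. Intervention requires a daily diary that includes concomitant treatments, and documentation of rescue medication in the eCRF.

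**The concern.** The definition describes an unexpected adverse reaction rather than an adverse event. It moves two assessments, whether the granule caused the event and whether the event was expected, from after recording to before it.

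In a double-blind trial, the sounder evidence on whether a product causes harm is the difference in all-cause event rates between the arms. One person's opinion about a single event is weaker evidence, and blinding limits what that person can know. If the opinion decides whether the event enters the database, the comparison is made only on what the opinion let through. An event that was left out leaves no trace, because the recorded items include neither of the two assessments. At stake are the completeness and interpretability of the clinical AE data, which are one part of the safety evidence.

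**Working it through.** The plan gives no figure on this point, so the main check is to apply the definition to each kind of event.

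**Step 1. What the definition lets through** (Adverse events; Colonoscopy and biopsies)

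| Event | Unexpected? | Attributed to granule? | Recorded as written? |
|---|---|---|---|
| Unexpected, attributed | yes | yes | yes |
| Expected, attributed | no | yes | no |
| Unexpected, considered unrelated | yes | no | no |
| Expected, considered unrelated | no | no | no |
| Harm from trial colonoscopy or biopsy | either | no | no |
| Any event in a healthy control | either | no (takes no granule) | no |

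One of the four combinations in treated patients qualifies. The last two rows concern identifiable people: 20 patients have a second colonoscopy with biopsies at week 12 and 10 healthy controls have one, so 20 + 10 = 30. In addition, patients without a colonoscopy in the year before enrolment have one at week 0; their number is not stated.

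**Step 2. How the two conditions could act in this trial.** Gut symptoms are easily put down to IBS-D itself and treated as unrelated. The Background cites a study of TXYF that found sporadic adverse events, so events of a known type could be treated as expected. Randomization and blinding keeps participants and outcome evaluators unaware of allocation, so attribution at a visit cannot draw on which product was taken.

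**Step 3. Size.** For events in treated patients:

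recorded share *s* = P(attributed to granule) × P(unexpected, given attributed)

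The documents give neither factor. Under assumed values:

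- 0.3 × 0.3 = 0.09
- 0.5 × 0.5 = 0.25
- 0.7 × 0.7 = 0.49
- 0.9 × 0.9 = 0.81

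The recorded share could thus be small or large.

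**Step 4. Effect on the comparison.** Let the true event rates be *a* (TXYF) and *b* (placebo). If *s* is the same in both arms, the recorded rates are *sa* and *sb*. The ratio *a/b* is unchanged, the difference shrinks to *s(a − b)*, and precision falls with the counts. If *s* differs between arms, the ratio is distorted as well. Blinding hides allocation but not the type of event. If the granule produces events of a kind regarded as expected, these are removed mainly from the TXYF arm; if it produces a distinctive and surprising event, that arm keeps relatively more. The direction cannot be settled from the documents.

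**Step 5. Severe and serious.** The Adverse events section lists severity as one descriptor of every event and also makes severe events the trigger for 24-hour reporting. The word therefore does two jobs. If SAEs are also read as a subset of AEs as defined, a grave event considered expected or unrelated could fall outside the rapid route too.

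**The case against.** The strongest reply is that blinding makes the filter largely non-differential. It then costs counts and precision but need not distort the ratio between arms. This stands as far as step 4 allows: equal filtering preserves the ratio but still shrinks the difference, and equality is not assured.

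A reader might infer that most untoward events will go unrecorded. The documents do not support that. They give no event rate and no share of events that are related or unexpected, and the range in step 3 includes 81% recorded.

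A reader might also infer that the safety aim cannot be met. That goes too far. The laboratory tests and ECG are done whatever the AE definition says, and the diary and eCRF capture concomitant and rescue treatment. These do not replace AE recording, since the laboratory tests fall only at baseline and week 12 and the diary is described as a check on compliance and diet, but they are safety-relevant data that survive. Nor do the documents support a claim that a detectable excess would become undetectable, since they give no AE rates from which to work out detectability.

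On SAEs, the standard abbreviation together with a 24-hour route to the ethics committee and regulator suggests loose English for serious. The team is committed to SOPs and GCP, and seriousness criteria and AE tabulation may sit in documents not shown. Their absence is no finding. Unblinding is also not confined to severe events, because other unpredictable events allow it. This limb is therefore a matter of terminology only.

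The reply that an article condenses the full protocol does not rescue the AE definition itself. The definition is an explicit rule, not an omitted detail.

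**Conclusion.** The point holds for the AE definition. Followed as written, it excludes expected events, events considered unrelated, harms of trial colonoscopies and biopsies, and every event in the 10 healthy controls. That lowers AE counts and weakens the between-arm clinical AE comparison that supports the safety aim. How much is lost is unknown; the 9% to 81% range rests on assumed probabilities only. The conclusion assumes that staff apply the definition literally and that no fuller document overrides it. The laboratory and ECG data are unaffected. The use of severe for SAE is secondary and calls for reconciled wording.

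**What to change.** In the Adverse events section, define an adverse event as any untoward medical occurrence after consent, whether or not expected and whether or not related to the study product. State that this covers the trial colonoscopies and biopsies and the healthy controls. In the eCRF, record severity, seriousness, expectedness and blinded causality as separate fields, completed after the event has been entered.

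Secondarily, reconcile the term severe adverse events in Adverse events, Randomization and blinding, and Abbreviations with the usual meaning of SAE, keeping severity as a descriptor of its own. This concerns terminology; whether it alters when unblinding is allowed is for the investigators to settle.

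The cost is a wording amendment, a few eCRF fields and slightly more event entry by research assistants who already record at every visit. The change is best made before events accrue, because events left unrecorded cannot be reliably recovered later.

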### Sample size calculation

The sample size calculation of this superiority trial depends on our previous pilot study and literature [9]. It can be speculated that the response rates of TXYF granule and placebo will reach 70% and 40%, respectively. We calculate by the software Gpower3.1 under the setting of 80% power and 5% type I error that 42 cases of each group are needed. With a drop-out rate of 15%, accumulated 100 cases are needed and we expect to recruit 120 IBS-D patients.

### Data management and monitor

Data management relies on a convenient follow-up system maintained by Empower Electronic Data Collection (EDC) (Solutions, Shanghai, China), and the company is also responsible for converting paper study diary and any other paper source documents (dietary questionnaire) to the electronic version. The collected data from participants will be kept absolutely secret, and the source data will be just accessible to the data administrator and statistician. All the paper source documentation about this trial will be properly preserved 5 years after the end of the trial.

Our group made up of a principal investigator, 3–5 clinicians, 2 research assistants, a data administrator, a drug manager, and a statistician will receive rigorous training and perform this trial in accordance with the Standard Operating Procedures (SOP) and Good Clinical Practice (GCP). This trial is unconditionally subject to the supervision and monitoring of the Science and Technology Department of the First Affiliated Hospital of Guangzhou University of Chinese Medicine. This independent department is responsible for the annual audit of our trial.

### Statistical analysis

#### Clinical data analysis

Based on the principle of intention-to-treat (ITT), all randomly assigned participants will be included in the statistical analysis. For participants who prematurely terminate this trial, outcomes of the last visit will be used as the final outcomes. Statistical analyses will be completed by SAS (version 9.4, SAS Institute, Cary, NC). Continuous variables will be presented in the form of means and standard deviations while the categorical variables will be presented in the form of counts and percentages. The primary outcome (week 4, week 8, week 12, and week 20) and the secondary outcome AR (week 12) will be assessed by using *χ*^2^ test or Fisher’s exact test. Another secondary outcome IBS-QOL (baseline, week 4, week 8, week 12, and week 20) will be assessed by using *T* test or Mann-Whitney *U* test accompanied with the Wilcoxon test. A two-sided *P* < 0.05 indicates statistical significance. For missing data, sensitivity analysis will be conducted and the optimal approach to the imputation of missing data will be proposed.

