### Outcome measurements

#### Primary outcome

The primary outcome of our trial is the response rate of IBS-Symptom Severity Score (IBS-SSS). A responder is defined as a 50% or more reduction in IBS symptoms compared to baseline [28]. IBS-SSS is a hitherto unique symptom severity questionnaire of IBS, which evaluates the condition of abdominal pain, abdominal distension, and defecation satisfaction. This definition of a responder that reports a 50% or more reduction in IBS symptoms is less disturbed by the initial severity of IBS. IBS-SSS will be assessed at baseline, week 4, week 8, week 12, and week 20 while the response rate of IBS-SSS will be assessed at week 4, week 8, week 12, and week 20.

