Limitations still exist in our study. Firstly, patients who underwent the first colonoscopy and biopsies may not want to have the second colonoscopy and biopsies after the treatment, especially for those with obvious remission of symptoms. We will fully communicate with them and give careful explanation and emphasize this point before the enrollment. Secondly, because of the long period of treatment and follow-up, we will encounter the problem of high drop-out rate and establishing close contact with participants is a must. In conclusion, we hope this trial will provide high-quality evidence on the effectiveness and safety of TXYF granule. We also expect to have more insight into the mechanism of IBS-D and find out specific biomarkers and pinpoint the targets of TXYF in IBS-D.

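### Carrying the last visit forward lets participants who left after week 4 or week 8 count as IBS-SSS responders at week 12 and at the off-treatment week 20

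*Protocol article*

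**What the plan says.** The section on clinical data analysis adopts intention-to-treat, under which "all randomly assigned participants will be included in the statistical analysis". It then fixes the handling of early leavers: "For participants who prematurely terminate this trial, outcomes of the last visit will be used as the final outcomes". The tests cover several visits: "The primary outcome (week 4, week 8, week 12, and week 20) and the secondary outcome AR (week 12) will be assessed by using" a chi-square or Fisher's exact test. The paragraph ends: "For missing data, sensitivity analysis will be conducted and the optimal approach to the imputation of missing data will be proposed".

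The primary outcome section gives the response criterion: "A responder is defined as a 50% or more reduction in IBS symptoms compared to baseline". It sets no condition that the participant is still in the trial at the visit concerned. IBS-SSS is measured at baseline and at weeks 4, 8, 12 and 20. The long-term efficacy section places week 20 two months after the end of treatment. Adequate relief (AR) is a count over weekly calls: a responder answers yes "for at least 6 of the 12 weeks".

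The sample size section plans for 15% drop-out. The Discussion describes IBS-D as recurrent and warns that "we will encounter the problem of high drop-out rate".

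**The concern.** The last-visit rule supplies the value that enters the main analysis, so it is a stated choice and not a detail left to an analysis plan. For a leaver, the week-12 result becomes a week-4 or week-8 result. The week-20 result becomes one taken on treatment, or at its end, although that visit exists to show what happens after treatment stops. The rule assumes that nobody relapses after leaving. The protocol's own account of the disease makes that doubtful: the Discussion gives recurrence as the reason for extending treatment to 12 weeks.

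If leavers differ between arms in number, timing or reason, the carried values can inflate or shrink the treatment difference, and the documents do not say which. The promised sensitivity analysis is the natural safeguard, but the sentence announcing it names no method, so it does not yet tell a reader how the main result will be tested.

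**Working it through.** **Inputs.** From the sample size section: response 70% v 40%, 80% power, 5% type I error, 42 per group, 15% drop-out, 100 needed, 120 to be recruited. Allocation is 1:1, so 60 per arm. The test is two-sided (clinical data analysis section). The response of drop-outs when last seen, and any unequal drop-out, are assumptions.

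**1. The plan's own figure.** Two proportions, pooled variance, no continuity correction:
n = [1.96·√(2·0.55·0.45) + 0.842·√(0.7·0.3 + 0.4·0.6)]² / 0.30² ≈ 42 per group.
42/0.85 = 49.4, so 50 per group and 100 in total. Both figures reproduce. At 60 per arm the same formula gives 92.1% power.

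**2. Who is affected.**
- Leaves before week 4: only the baseline score exists, so the carried reduction is 0% and the person is a non-responder under LOCF and under the proposed rule.
- Leaves after week 4 or week 8 as a responder: counted as a responder at weeks 12 and 20.
- Leaves after week 12 as a responder: week 12 is observed; week 20 is carried.

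**3. Upper bound.** 0.15 × 60 = 9 per arm; 9/60 = 15 points. The bound is reached only if all nine leave after an IBS-SSS visit that showed response.

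**4. Equal 15% drop-out, completers at 70% v 40%.** Arm rate = 0.85 × completer rate + 0.15 × rate assigned to drop-outs; power at 60 per arm.

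| Drop-outs counted as responders (TXYF / placebo) | Rates | Difference (points) | Power |
|---|---|---|---|
| 70% / 40% | 70.0% v 40.0% | 30.0 | 92.1% |
| 50% / 30% | 67.0% v 38.5% | 28.5 | 88.8% |
| 40% / 40% | 65.5% v 40.0% | 25.5 | 80.7% |
| 0% / 0% (non-response) | 59.5% v 34.0% | 25.5 | 80.7% |

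**5. Unequal drop-out, same completer rates.**
- 20% TXYF, 10% placebo, as non-response: 0.80 × 70% = 56% v 0.90 × 40% = 36%; 20 points, power 59.6%.
- 10% TXYF, 20% placebo, as non-response: 63% v 32%; 31 points, power 93.5%.
- LOCF with drop-outs last seen at 70% / 40% shows 30 points in both cases.

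**6. Direction, with no difference among completers (40% in both arms).** If 70% of drop-outs in each arm were responders when last seen, LOCF gives 46% v 43% (+3 points) with 20% TXYF and 10% placebo drop-out, and 43% v 46% (−3 points) with the proportions reversed. The sign follows the drop-out pattern.

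**7. AR.** If the last weekly answer were carried forward, a yes in week k followed by withdrawal would fill weeks k to 12, that is 13 − k weeks. This is at least 6 when k ≤ 7. If unanswered weeks are not filled, a single yes stays 1 of 12.

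**The case against.** **Non-response is also a single imputation.** Counting leavers as failures assigns one fixed value to every drop-out, just as LOCF does. This stands as far as it goes. The proposed rule is defensible only if stated as part of the definition of response (in the trial at that visit and at least 50% better), not as a guess at an unseen score. It also reacts to unequal drop-out: in step 6 it would give 32% v 36% and 36% v 32%. That is why the sensitivity analyses are needed.

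**A sensitivity analysis is already promised.** True, and naming its model is commonly left to an analysis plan. A reader might infer from "the optimal approach to the imputation of missing data will be proposed" that the main method will be chosen after the data are seen. The text does not support that: the main rule is fixed, the sentence concerns the sensitivity analysis, and the randomisation section keeps data analysts blinded. What remains is that the method is open.

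**AR.** A reader might infer that someone who leaves in week 1 after one yes becomes an AR responder. The rule does not say how a last visit applies to weekly calls, so this is one possible reading. The point is an ambiguity to close.

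**Size.** Suppose 20% v 10% drop-out, with 60% v 35% of leavers responding when last seen. LOCF then shows a difference 0.20 × 60 − 0.10 × 35 = 8.5 points larger than non-response counting (28.5 v 20). A reader might take this as the bias of LOCF. It is the gap between two single imputations, with neither known to be true. Likewise, 15 points is a limit and not an expected shift, since early leavers are non-responders under both rules.

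**Conclusion.** The point holds for the IBS-SSS response rate. The stated rule counts participants who improved by week 4 or 8 and then left as responders at weeks 12 and 20, and at week 20 it substitutes an earlier result for the off-treatment outcome. The protocol's description of the disease as recurrent and its expectation of high drop-out make this more than a formality.

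The effect on the treatment difference has no known direction. Its limit is 15 points per arm at 15% drop-out, against a planned difference of 30, and the likely shift is smaller. The power figures assume that 70% and 40% are completer rates, which the sample size section does not say. The sample size calculation itself is not at fault. This is a weak primary rule that is cheap to improve.

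**What to change.** 1. Replace the last-visit rule for the responder outcomes: a participant with no IBS-SSS at the analysed visit, weeks 12 and 20 in particular, is a non-responder at that visit. State this as a composite definition of response.
2. Replace the sentence on an optimal approach with named sensitivity analyses: multiple imputation by arm from baseline and observed IBS-SSS scores, with response derived from the imputed score, and a tipping-point analysis.
3. For AR, state that an unanswered week counts as no.

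**Cost.** Wording and some programming, with no added recruitment if drop-out is equal at 15%. Response rates will look lower in both arms. With 70% and 40% as completer rates, power at 60 per arm falls from 92% nominal to about 81% at equal 15% drop-out, and to about 60% if drop-out is 20% on TXYF and 10% on placebo. Both figures should be stated with the rule.

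### The primary outcome is tested at four visits with no primary visit and no rule for success, while the sample size assumes one test at 5%

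*Protocol article*

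**What the plan says.** - **Outcome definition.** Under Primary outcome: "The primary outcome of our trial is the response rate of IBS-Symptom Severity Score (IBS-SSS"). A responder has at least a 50% reduction from baseline. The same section adds that "the response rate of IBS-SSS will be assessed at week 4, week 8, week 12, and week 20". No visit is singled out.
- **Analysis.** Clinical data analysis repeats the four weeks, "The primary outcome (week 4, week 8, week 12, and week 20"), assigns a chi-square or Fisher's exact test, and sets one threshold: "A two-sided *P* < 0.05 indicates statistical significance". The same sentence gives adequate relief a single visit, week 12.
- **Sample size.** The assumption is that "the response rates of TXYF granule and placebo will reach 70% and 40%, respectively", and the trial is sized "under the setting of 80% power and 5% type I error that 42 cases of each group are needed". With 15% drop-out this becomes 100, and 120 are to be recruited. No visit is attached to the two rates.
- **Week 20 again.** Long-term efficacy assessment, a subsection of the secondary outcomes, says of the week 20 visit that "IBS-SSS response rate and IBS-QOL will be evaluated".
- **Multiplicity.** The only adjustment described is Benjamini-Hochberg, under Mechanistic data analysis, for the transcriptome data.

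**The concern.** The design section and the analysis section describe different trials. One is a single comparison at 5%. The other is four comparisons of the primary outcome, each judged at 5%, with nothing said about how four answers become one.

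If the visits disagree, the article cannot say whether the trial succeeded. A significant result at week 4 alone, or at week 20 alone (8 weeks after treatment ends), could be presented as the primary result. The double listing of week 20 adds to this, because the same test is both primary and secondary. What is at stake is the error rate behind the main efficacy claim, and the reader's ability to tell a planned result from a selected one.

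**Working it through.** **Inputs from the article.** Response rates 0.70 and 0.40, two-sided alpha 0.05, power 80%, 1:1 allocation, 15% drop-out, 120 recruited, four test visits. **Assumed input.** The correlation between the test statistics at different visits is not given, so I take a common value from 0.5 to 0.9, with 0 as the upper reference.

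**1. Reproduce the stated sample size.** With the pooled rate (0.70 + 0.40)/2 = 0.55:

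n = [1.960·√(2·0.55·0.45) + 0.842·√(0.70·0.30 + 0.40·0.60)]² / 0.30² = 41.97, so 42 per group.

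42/0.85 = 49.4, so 50 per group and 100 in total. The article's figures reproduce as one two-sided test at 0.05.

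**2. Error if any visit counts as success.** For k independent tests, the chance of at least one false positive is 1 − 0.95^k:

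- k = 4: 1 − 0.95⁴ = 18.5%
- k = 3 (week 20 secondary only): 1 − 0.95³ = 14.3%

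For correlated visits I took jointly normal test statistics with common correlation ρ. The chance that at least one |Z| exceeds 1.96, and the chance that at least one Z exceeds 1.96 in favour of TXYF, are:

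| ρ | 4 visits, either direction | 3 visits, either direction | 4 visits, favouring TXYF |
|---|---|---|---|
| 0.5 | 15.6% | 12.5% | 7.8% |
| 0.7 | 13.0% | 10.9% | 6.5% |
| 0.8 | 11.4% | 9.8% | 5.7% |
| 0.9 | 9.4% | 8.4% | 4.7% |

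The reference values for one test are 5% in either direction and 2.5% in favour of TXYF.

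**3. Cross-check with binary data.** I simulated responders with 60 per arm, a 40% rate in both arms at all four visits, and a latent correlation of 0.5 to 0.9. At least one significant test occurred in about 17% (0.5) down to 13% (0.9) of trials, while one visit alone rejected in about 5%. These figures are somewhat higher than the table because dichotomising the score weakens the correlation between visits.

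**4. What each repair does to power for 70% v 40%.**

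| Evaluable per arm | One visit at 0.05 | Each of four visits at 0.05/4 = 0.0125 |
|---|---|---|
| 42 | 80% | 61% |
| 51 (60 less 15%) | 87% | 72% |
| 60 | 92% | 80% |

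With Bonferroni over four visits the same formula gives 59.9, so 60 evaluable per arm. After 15% drop-out that is 60/0.85 = 70.6, so 71 per arm or 142 in total, more than the 120 planned.

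**The case against.** **The inflation depends on a rule that is not written.** A reader might infer that the trial's type I error is 18.5%, or that the stated 5% simply fails. The article supports neither. It never says that one significant visit is enough. If all four visits had to be significant, the error would not exceed 5%. This objection stands, and the percentages are conditional. What remains is that no rule is stated, so 5% is not assured.

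**Independence is unrealistic.** The same patients are compared with the same baseline, and carrying the last visit forward makes later visits more alike. This also stands, so 18.5% is only an upper reference. Even at a correlation of 0.9 the four-visit figure is nearly double 5%.

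**Week 12 may be what is meant.** It is the end of treatment and the visit for adequate relief. But the sentence that gives adequate relief one visit gives the primary outcome four. The sentence on using the last visit concerns participants who stop early. The Discussion also gives better long-term efficacy as a reason for the longer treatment, so week 12 cannot be taken as settled.

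**The statistical analysis plan may settle it.** A hierarchy may exist there, so one can say only that the article states none. The point does not rest on silence, however. The article itself fixes four tests of the primary outcome, a common threshold, a single-test sample size and two roles for week 20.

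**Conclusion.** The point holds in this form: the article defines no primary visit and no success rule for a primary outcome tested four times, and its sample size matches only one of those tests. Week 20 is classed as both primary and secondary.

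The consequence has a size only under an any-visit reading and an assumed correlation of 0.5 to 0.9. Then the false-positive chance is about 9% to 16% with four visits and about 8% to 13% with three. In favour of TXYF alone it is about 4.7% to 7.8% with four visits.

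A reader might also infer that the sample size is miscalculated. It is not: 42 per group and 100 in total are correct for one test. Nor does the text show that the sponsor intends to pick the most favourable visit. It only leaves that possible. Because this bears on the trial's main claim and is cheap to repair, it should be corrected before unblinding.

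**What to change.** Before unblinding, amend the protocol and analysis plan as follows:

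1. Name one visit as the primary time point for IBS-SSS response, tested at two-sided 0.05. Week 12, the end of treatment, is the natural candidate, but the choice is the sponsor's.
2. State that the 70% and 40% rates refer to that visit.
3. If week 12 is chosen, list week 20 response only under long-term efficacy and remove it from the primary outcome text.
4. Make the remaining visits supportive. Either report them descriptively, or test them in a stated order (for example week 12, then 20, then 8, then 4), each at 0.05 and only while every preceding test is significant. Testing three visits in parallel after week 12 would not control the error among them.

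**Cost.** This is a change of wording and needs no additional patients. The 42 per group stands at 80% power. Power is 87% at 51 per arm and 92% with all 60 per arm evaluable, provided that 70% v 40% holds at the named visit. The price is that a significant result at another visit alone can no longer be claimed as primary success, so some power is given up relative to an any-visit rule.
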